### Statistical analyses

All statistical analyses will be performed with IBM SPSS Statistics 21.0. For continuous variables, independent t-tests will be used to determine inter-group differences and Man–Whitney U-tests for intra-group comparison, while the χ^2^ or an equivalent test is to be used to determine the associations between categorical variables. Because this is a prospective RCT involving repeated measures, repeated measures analyses of variance will be applied to determine significant differences within the study groups. We also considered the possible effect of time on groups. The evaluation of the intervention is based on an intention-to-treat analysis. A *p*-value of 0.05 has been set as the level of significance.

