## Methods

### Study design

This study describes a two-armed, matched-design, web-based RCT. The nutrition education programme that we have developed as part of a health promotion project (Fig. 1). The intervention period is 5 weeks. The RCT is designed in line with the CONSORT statement for randomised trials of non-pharmacologic treatment [28]. Participants were assessed at three points in time: at baseline (T1), at post intervention (5 weeks later; T2), and at a follow-up at 3 months (T3). The participants were randomly assigned to one of two conditions: the intervention group and the waiting list group (i.e., the control group).

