### Assessment

The primary outcome variable was assessed using a self-administered questionnaire in Japanese. Regarding the assessment, at baseline (T1), primary outcomes, transtheoretical model [31], self-efficacy [32], dietary knowledge [33], perceptions of neighborhood food environments within secondary outcomes, and all other measurements. After completion of the 5-week intervention, participants received an e-mailed request to participate in the post-intervention survey (T2). At post-intervention survey (T2), we assessed the all primary outcomes, all secondary outcomes, all other measurements excluding the subjective economic status. We evaluated about the participants’ satisfaction of process evaluation as after intervention. Finally, participants received another e-mail request to participate in a follow-up survey 3 months after completing the intervention (T3). At follow-up survey (T3), we assessed the all primary outcomes, all secondary outcomes, and all other measurements excluding the subjective economic status.

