### Sample size

The sample size was calculated using G*Power [50]. We set an effect size of 0.5, an α of 0.05, and a power of 0.95. With the expectation that two-thirds of participants would drop out, the size of the intervention group was set at 900 subjects, while that of the control group was set at 600 subjects with the expectation that a half of participants would drop out. Furthermore, we aimed to divide the intervention and control groups further according to income (low and high).

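### The between-arm method named for continuous outcomes is an independent t-test, and no stated analysis adjusts for the participant's own T1 value, although T1 is collected

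*Protocol article*

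**What the plan says.** The Statistical analyses section names the between-arm method: "For continuous variables, independent t-tests will be used to determine inter-group differences". The method for repeated measurements is given a different task: "repeated measures analyses of variance will be applied to determine significant differences within the study groups". One further sentence touches on arm and time together: "We also considered the possible effect of time on groups". No covariate, change score or time point is named for the t-test. The same section adds: "The evaluation of the intervention is based on an intention-to-treat analysis" and "A *p*-value of 0.05 has been set as the level of significance".

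Baseline values exist. Study design: "Participants were assessed at three points in time: at baseline (T1), at post intervention (5 weeks later; T2), and at a follow-up at 3 months". The Assessment section includes the primary outcomes in the T1 survey: "Regarding the assessment, at baseline (T1), primary outcomes, transtheoretical model [31], self-efficacy [32], dietary knowledge [33".

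The Sample size section expects heavy and unequal loss: "With the expectation that two-thirds of participants would drop out, the size of the intervention group was set at 900 subjects". The control group is set at 600 with half expected to drop out. It also plans to divide each arm into low and high income.

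**The concern.** Each participant's T1 value predicts that person's T2 and T3 values. A between-arm comparison that does not condition on T1 leaves that predictable variation in the error term, so the estimate is less precise than the collected data allow.

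The second issue is imbalance. Randomisation balances T1 among those allocated, but the plan expects to keep one third of one arm and half of the other. If staying in is related to T1, completers can differ at T1. A comparison of T2 values carries part of that gap into the effect, and a comparison of changes carries the remainder with the opposite sign.

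At stake are the precision of the main comparison when the true effect is modest, the low/high income comparisons that serve the secondary objective, and one avoidable component of bias.

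**Working it through.** **Inputs from the article:** effect size 0.5, α 0.05, power 0.95; 900 allocated with two-thirds loss; 600 allocated with half lost (Sample size).

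**Assumptions:** T1–T2 correlation ρ = 0.5, range 0.3 to 0.7; two-sided test; equal SD at T1 and T2; equal income split.

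**The plan's own figure.** A two-sample t-test with the stated inputs needs 105 per arm, which inflates to 105/(1/3) = 315 and 105/(1/2) = 210, not 900 and 600. That mismatch is a separate matter. Here I use the completers that the plan expects: 900 × 1/3 = 300 and 600 × 1/2 = 300, or 150 per arm in each income half.

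**Variance of the between-arm difference, relative to a t-test on T2 values (= 1):**

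- change score, which is also the T1-to-T2 contrast of an arm-by-time test: 2(1 − ρ)
- ANCOVA on T1: 1 − ρ²
- ratio of change score to ANCOVA: 2/(1 + ρ)

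| ρ | T2 values | Change | ANCOVA | Cut v T2 values | Change ÷ ANCOVA |
|---|---|---|---|---|---|
| 0.3 | 1 | 1.40 | 0.91 | 9% | 1.54 |
| 0.5 | 1 | 1.00 | 0.75 | 25% | 1.33 |
| 0.7 | 1 | 0.60 | 0.51 | 49% remaining gap closed to 51% of the original variance, a cut of 49% | 1.18 |

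**Power.** Two-sample t power, with the standardised effect d divided by the square root of the factor above:

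| Setting | T2 values | ANCOVA, ρ = 0.3 / 0.5 / 0.7 |
|---|---|---|
| d = 0.20, 300 per arm | 68.6% | 72.7 / 80.6 / 92.8% |
| d = 0.30, 150 per arm | 73.6% | 77.5 / 84.9 / 95.2% |
| d = 0.50, 300 per arm | over 99.9% | over 99.9% |
| d = 0.50, 150 per arm | 99.1% | higher still |

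A change-score analysis at d = 0.20 with 300 per arm has 68.6% power at ρ = 0.5, the same as the t-test on T2 values, and 88.4% at ρ = 0.7.

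**Imbalance through T1.** If completers differ by b SD at T1, a T2 comparison is off by ρb and a change comparison by −(1 − ρ)b; conditioning on T1 removes this part. With b = 0.1 and ρ = 0.5 the errors are +0.05, −0.05 and 0 SD.

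**What adjustment can and cannot do.** Simulated completer analyses (900 to 300, 600 to 300, no true effect, ρ = 0.5) rejected as follows:

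| What staying in depends on | T2 t-test | Change | ANCOVA |
|---|---|---|---|
| T1 only, correlation 0.3 | 8.4% | 8.3% | 5.1% |
| T1 only, correlation 0.5 | 15.6% | 15.5% | 5.1% |
| Only the part of T2 not explained by T1, correlation 0.3 | 16.5% | 16.7% | 20.4% |

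The first two rows show the benefit when dropout depends only on T1. The third shows ANCOVA doing somewhat worse than the other two under another mechanism. The article gives no mechanism.

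**The case against.** An unadjusted t-test in a randomised trial is a valid test, so this is a gain in efficiency and not the repair of an error. That stands, as does the point that power at 0.5 is already ample.

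A reader might infer that the plan discards T1 altogether. The text does not establish that. The t-test could be run on changes, and the sentence on time and groups could mean an arm-by-time test; both use T1. Neither adjusts for it, however. Both amount to a change comparison, whose variance exceeds that of ANCOVA by a third at ρ = 0.5.

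A reader might also infer that the named test inflates false positives and that ANCOVA restores 5%. That holds only when dropout depends on T1 alone. Under other dropout ANCOVA can do as badly or worse, so the simulated rates are not a general claim. They also describe completers, whereas the article states intention-to-treat; how missing values are handled may properly sit in a fuller plan.

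Finally, the article gives no response scale for self-rated health. If it is analysed as categorical, the linear model does not apply to it.

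That an analysis plan might specify ANCOVA does not remove the point: the article names a between-arm method, so such a plan would depart from it.

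**Conclusion.** The point holds as an inexpensive improvement to a method that the article states. No reading of the Statistical analyses section adjusts the between-arm comparison for T1. Under the assumed correlations, ANCOVA leaves 91%, 75% or 51% of the variance of a t-test on T2 values (ρ = 0.3, 0.5, 0.7). The gain matters for true effects well below 0.5 and for the income halves, not for the planned effect size. The advantage over a change-score reading is smaller at high correlation.

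With the expected unequal dropout, adjustment also removes whatever imbalance runs through measured T1. The documents do not support a wider claim that it protects against differential dropout. The sizes rest on an assumed correlation, 300 completers per arm and an equal income split.

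**What to change.** In Statistical analyses, replace the sentence on independent t-tests for inter-group differences with wording to this effect: for each outcome analysed as continuous and measured at T1, the arms will be compared at T2 and at T3 by a linear model (ANCOVA, or an equivalent mixed model) with arm and the participant's own T1 value; the adjusted difference will be reported with its 95% confidence interval, and the independent t-test kept as a supportive unadjusted analysis. Sex, age and household income are optional covariates. Clarify in the same place what the repeated measures ANOVA is for.

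The cost is a sentence or two. T1 is collected before allocation, so it should be available for everyone randomised, and SPSS fits the model. No extra participants or surveys are needed. The handling of missing T2 and T3 values under intention-to-treat still has to be settled separately.

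### Mann-Whitney, an independent-samples test, is named for within-group comparison, and the repeated-measures ANOVA does not clearly name the group-by-time contrast

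*Protocol article*

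**What the plan says.** Three procedures for continuous outcomes appear in the protocol article under Statistical analyses.

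- Between arms: "independent t-tests will be used to determine inter-group differences".
- Within arms: "Man–Whitney U-tests for intra-group comparison".
- Over time: "repeated measures analyses of variance will be applied to determine significant differences within the study groups", followed by "We also considered the possible effect of time on groups".

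The same section bases the evaluation on intention to treat and sets a significance level of 0.05.

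Under Study design, "Participants were assessed at three points in time: at baseline (T1), at post intervention (5 weeks later; T2), and at a follow-up at 3 months", and "The participants were randomly assigned to one of two conditions: the intervention group and the waiting list group (i.e., the control group". Each participant therefore contributes up to three values, and only the comparison of arms is randomised. The Assessment section lists the primary outcomes among the T1 measures.

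**The concern.** There are two faults of unequal weight.

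1. Mann-Whitney assumes two independent samples. Applied to T1 against T2 in the same people, it ignores the correlation between the two values. The variance it assumes for the comparison is then too large, so its p-values are too big and real change within an arm is missed more often than need be.
2. Change within one arm mixes any programme effect with whatever moves both arms, such as answering the same questionnaire again, season, or regression to the mean. In a repeated-measures ANOVA with two arms, the term that isolates the programme is group by time. The stated purpose of the ANOVA is differences within groups, and the next sentence is too vague to establish that group by time is the test meant.

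A smaller matter is that the planned between-arm t-test makes no use of the T1 value. That costs precision but is not an error.

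**Working it through.** **Inputs.** The Sample size section has "With the expectation that two-thirds of participants would drop out, the size of the intervention group was set at 900 subjects", and sets the control arm at 600 with half expected to drop out. Expected completers are 900 × (1 − 2/3) = 300 and 600 × (1 − 1/2) = 300. The same section says "We set an effect size of 0.5, an α of 0.05, and a power of 0.95", without naming the type of effect size. The T1-T2 correlation ρ is not in the document; it is an assumption, shown from 0 to 0.7. Normal data are also assumed. The plan gives no operating figure for the within-group test, so there is none to reproduce.

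**Step 1: type I error of Mann-Whitney on paired data.** The test assumes a variance proportional to 2, whereas the true one is proportional to 2(1 − ρ). The actual two-sided error at nominal 5% is therefore about 2[1 − Φ(1.96/√(1 − ρ))].

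- ρ = 0.3: 1.96/√0.7 = 2.34, giving 1.9%.
- ρ = 0.5: 1.96/√0.5 = 2.77, giving 0.6%.
- ρ = 0.7: 1.96/√0.3 = 3.58, giving 0.03%.

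**Step 2: simulation.** 4,000 runs per setting, 300 pairs, bivariate normal data, nominal 5%:

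| ρ | Mann-Whitney type I error | Signed-rank type I error | Mann-Whitney power, 0.2 SD | Signed-rank power, 0.2 SD |
|---|---|---|---|---|
| 0 | 5.1% | 5.7% | 0.67 | 0.67 |
| 0.3 | 1.9% | 4.7% | 0.69 | 0.81 |
| 0.5 | 0.6% | 5.2% | 0.73 | 0.92 |
| 0.7 | 0.1% | 4.7% | 0.77 | 0.99 |

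The simulation agrees with the formula. At ρ = 0.7 the simulated 0.00125 is 5 runs out of 4,000, so only its order of magnitude counts.

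**Step 3: a change as large as the design effect.** Take 0.5 as a change in SD units, and use the efficiency of rank tests on normal data, √(3/π) = 0.977. The expected Mann-Whitney statistic is 0.977 × 0.5 × √(300/2) = 5.98. Power is Φ((5.98 − 1.96)/√(1 − ρ)), which is at least Φ(4.02), or above 0.999, for any ρ from 0 upwards. The loss is confined to smaller changes.

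**Step 4: why the contrast must be named.** Let both arms shift by 0.15 SD with no programme effect, at ρ = 0.5 (shift and correlation both assumed). In 4,000 runs with 300 per arm, a paired within-arm test is significant in the intervention arm 73% of the time, and in that arm alone 20% of the time. The between-arm test of change rejects 4.8%. A one-arm repeated-measures ANOVA at two time points is the same as the paired t-test, so the first two figures also describe an ANOVA run within each arm on T1 and T2.

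**Step 5: using T1 in the between-arm comparison.** Relative to the follow-up-only t-test (variance 1):

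- ANCOVA on T1 has variance 1 − ρ²: 0.75 at ρ = 0.5 and 0.51 at ρ = 0.7, that is 25% and 49% lower.
- The difference in change, which is group by time at two time points, has variance 2(1 − ρ): 1.4 at ρ = 0.3, 1.0 at 0.5 and 0.6 at 0.7.

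The 25% and 49% therefore belong to ANCOVA. The group-by-time contrast is valid but gains precision only when ρ exceeds 0.5.

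**The case against.** **A valid test is planned.** A reader might infer that the trial has no sound test of its programme. The document does not support that. Under randomisation the independent t-test between arms is valid without baseline adjustment. With 300 completers per arm its power for a standardised difference of 0.5 exceeds 0.999. This objection stands in full.

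**The time-and-group sentence may mean group by time.** Coming straight after the repeated-measures ANOVA, that is a plausible intention. It stands as a reason to call the fault unclear wording rather than a wrong analysis. It does not remove the need to name the contrast, because the sentence before it points the ANOVA within groups.

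**Intra-group could mean low against high income within an arm.** The Sample size section plans such a division, and those would be independent samples for which Mann-Whitney is valid. The Statistical analyses section does not say so, and change over time is the more natural reading. On the income reading, a comparison inside one arm would still not show whether the effect differs by socio-economic status, which is the secondary objective.

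**Drift credited to the programme.** A reader might also infer that the authors will claim benefit from within-arm p-values. Nothing in the document says they will. The 73% in step 4 comes from a paired analysis under an assumed shift; it shows why the contrast should be named and does not predict what this trial will report.

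**The Mann-Whitney error is conservative.** That is so: it hides change within an arm and does not produce false claims. It also touches only within-arm comparisons.

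**Conclusion.** On the natural reading, one stated rule is wrong and another is unclear. Mann-Whitney is unsuited to change within a group. For any positive correlation it is conservative; for a 0.2 SD change at assumed correlations of 0.3 to 0.7 it gives up 0.12 to 0.22 of power (0.81 − 0.69 and 0.99 − 0.77), and for a 0.5 SD change practically nothing. The ANOVA wording leaves it uncertain whether group by time is the test intended.

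The trial's ability to test its programme is not in doubt, because the between-arm t-test is valid. Baseline adjustment is a free gain in precision, not the correction of an error. The point deserves correction before analysis but is not a fatal defect. The sizes rest on assumed correlations, normal data and the dropout the plan expects; the direction of the Mann-Whitney error needs only a positive correlation.

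**What to change.** Change the Statistical analyses section as follows.

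1. For change within a group, replace Mann-Whitney by the Wilcoxon signed-rank test or the paired t-test, and label these results descriptive. If low against high income within an arm was meant, say so, and test arm by income for the secondary objective.
2. State that the programme effect is judged by the between-arm difference at T2 and at T3, with a 95% confidence interval. Take it either from an ANCOVA adjusted for T1, for outcomes with a T1 value, or from the group-by-time term of the repeated-measures ANOVA, reported as the T1-to-T2 and T1-to-T3 contrasts. ANCOVA is the more precise of the two.
3. Reword the two ANOVA sentences so that group by time is named and within-group differences are no longer given as the purpose.

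The cost is a few sentences. No new data or participants are needed, and these are standard procedures in the software the plan names.

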### Study sample

#### Recruitment source and procedure

A web-based intervention survey was conducted by a Japanese online research service company that contains data, including sociodemographic attributes, for approximately 160,300 adults aged 30–59 years. Participants were randomly selected based on Japanese population statistics for the present study. We targeted adults because of the necessity of health promotion, healthy eating, and reduction in health disparities for this age group [23]. The following inclusion criteria are considered: (1) men and women aged 30–59 years old; (2) able to understand Japanese; (3) can access the Internet at home, work, or a public place; (4) agree to access the study website during the 5-week intervention period; (5) will participate in all three assessment points during the 4-month study period. The exclusion criterion is having an household income of ten million yen or more (meaning that 88.4% of the total population is having an household income of ten million yen less) [29]. The study procedure from enrolment to follow up is depicted in Fig. 1.

The research company that we used in the present study periodically analyses and updates its registrant database. A notable characteristic of this company is that, to prevent bias among survey respondents, the firm requests the participation of the minimum number of respondents after taking response rate into consideration. Moreover, once every 6 months, the firm updates its monitoring information and conducts checks to safeguard against double registration or non-existent IP addresses. Registrants had been enrolled with the survey company by an open recruitment process.

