Study participants were recruited using the following procedure. Of the approximately 160,300 registered monitors (as of September 2015), participants randomly to match the sex, age [30], and household income [29] distributions of Japan. Only study participants received an e-mail containing the website URL and password. Participate in the study were randomly assigned it to two groups in the order that received an answer to the intervention or control groups by the online research service company. The web-based nutrition educational programme is available in HTML format. Respondents who completed the questionnaire and clicked the ‘send’ button at the end of the online informed consent form were considered to have consented to survey participation (*n* = 1500). The research service company offered reward points valued at 40 JPY (in October 2015, one USD was equivalent to approximately 121 JPY) at T1. Of these, individuals who were allocated to the intervention group were offered reward points valued at 300 JPY after completion of the intervention (T2). Respondents from the control group were offered reward points valued at 40 JPY at T2. The participants were again offered reward points valued at 40 JPY for completing the assessment at 3 months after the completion intervention (T3; i.e. 4 months after the completion of the baseline survey [T1]).

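### Intention-to-treat is declared, but the named tests drop participants with missing outcomes unless these are imputed, and 67% versus 50% dropout is expected

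*Protocol article*

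**What the plan says.** The Statistical analyses section sets the principle: "The evaluation of the intervention is based on an intention-to-treat analysis". It also fixes the methods, to be run in SPSS 21.0. "For continuous variables, independent t-tests will be used to determine inter-group differences", with Mann–Whitney tests within groups and χ² or equivalent tests for categorical variables. For the repeated data, "repeated measures analyses of variance will be applied to determine significant differences within the study groups", and a possible effect of time on groups is mentioned. It names no imputation, mixed model or other device for participants without follow-up data.

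The Sample size section anticipates very heavy and unequal loss. "With the expectation that two-thirds of participants would drop out, the size of the intervention group was set at 900 subjects", while "the control group was set at 600 subjects with the expectation that a half of participants would drop out". It does not say whether this loss refers to the 5-week survey (T2) or the 3-month follow-up (T3).

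Two statements under Recruitment source and procedure also bear on who responds. One inclusion criterion is that the person "will participate in all three assessment points during the 4-month study period". The T2 reward differs by arm: 300 JPY in the intervention group and 40 JPY in the control group.

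**The concern.** Intention-to-treat means comparing everyone randomised in the arm to which they were assigned. An independent t-test can use only people who have the outcome. Classical repeated-measures ANOVA keeps only people with every visit present. With 60% of outcomes expected to be missing, the treatment of missing data largely determines the result, and the tests fixed in the article do not treat it at all.

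The 3:2 allocation evens out the expected number of completers but not their comparability. The people left would be one third of one arm and one half of the other. If the reasons for staying relate to diet-related quality of life, self-rated health or eating behaviour, the comparison is no longer protected by randomisation. The Strengths and limitations section relies on that protection, saying that confounding is mostly removed at allocation. It mentions possibly low adherence as a limitation, but not attrition bias.

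**Working it through.** **Inputs.** From Sample size: 900 and 600 randomised; dropout 2/3 and 1/2; effect size 0.5, α 0.05, power 0.95. The effect size is read here as a standardised mean difference, which is an assumption.

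**1. The plan's own figure.** A two-sided t-test with these inputs needs 105 per arm. Allowing for dropout gives 105 ÷ (1/3) = 315 and 105 ÷ (1/2) = 210. Doubling for two income strata gives 630 and 420. One-sided, with 88 per arm, the figures are 264 and 176, or 528 and 352 doubled. None of these is 900 and 600. That is a separate matter on which this point does not depend. The stated sizes do correspond to equal completer numbers:
- intervention: 900 × 1/3 = 300
- control: 600 × 1/2 = 300
- total: 600 / 1500 = 40%
- retention: 33.3% v 50.0%, a gap of 16.7 percentage points.

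Power for a difference of 0.5 SD with 300 v 300 is above 0.999, so the threat is bias and not lost power.

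**2. Illustration: unadjusted follow-up t-test, no true effect.** Assume that people stay if a standard-normal engagement score lies in the top 1/3 (intervention) or top 1/2 (control), and that engagement correlates r with the outcome (SD 1).
- The mean of the top fraction p is φ(c)/p, where c is the cut-off. For p = 1/3, c = 0.431 and the mean is 0.3636 ÷ 0.3333 = 1.091. For p = 1/2, c = 0 and the mean is 0.798.
- The difference in engagement is 1.091 − 0.798 = 0.293, so the spurious outcome difference is 0.293 × r.
- Engagement variance after selection is 0.280 and 0.363. Outcome variance is 1 − r²(1 − 0.280) and 1 − r²(1 − 0.363), and SE = √(sum of the two ÷ 300).
- Type I error is Φ(λ − 1.96) + Φ(−λ − 1.96), with λ = difference ÷ SE.

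| r | Spurious difference (SD) | SE | λ | Type I error |
|---|---|---|---|---|
| 0.2 | 0.059 | 0.0805 | 0.73 | 11.2% |
| 0.3 | 0.088 | 0.0791 | 1.11 | 19.9% |
| 0.5 | 0.146 | 0.0744 | 1.97 | 50.3% |

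**3. Change scores.** In a group-by-time test, r has to be the correlation of engagement with change. If engagement correlates equally with the outcome at T1 and at follow-up, and the SDs are equal, its covariance with change is zero and the spurious difference cancels. The table therefore does not apply to that test.

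**4. Other scenarios.** If dropouts differ from completers by k SD equally in both arms, the bias is k × (2/3 − 1/2) = k/6. For k = 0.25 to 1.0 this is 0.04 to 0.17 SD. As an outer bound, suppose selection is monotone, the outcome is normal and the excess third of control completers is trimmed from one tail. The difference then moves by φ(0.431) ÷ (2/3) = 0.3636 ÷ 0.6667 = 0.545 SD in either direction. That exceeds the planned effect of 0.5.

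**The case against.** The strongest reply is that this is a condensed article. How missing data are handled is commonly left to an analysis plan, and none is shown. Nothing in the article says that only completers will be analysed, and imputation before the named tests would be compatible with its wording. That part stands, so a reader should not conclude that intention-to-treat is impossible under this plan. It does not remove the point. The article itself chose the tests, declared the principle and sized the arms for the loss, and nothing in it indicates that imputation is intended.

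Several stronger readings are tempting but not supported.
- **That the main result would rest on 40% of participants.** No main analysis is named. The ANOVA is tied to differences within groups. A t-test at T2 uses everyone with T2 data. The 40% applies only at the unstated time point to which the dropout refers.
- **That the bias favours the programme.** This follows only if the more engaged stay and do better. The article does not say who drops out; people who already eat well might leave.
- **That the T2 reward selects adherers.** The wording "individuals who were allocated to the intervention group were offered reward points valued at 300 JPY after completion of the intervention (T2" may only mark the time. The Intervention group section uses similar wording for when the T2 request was sent, with no adherence condition. If paid regardless of adherence, the larger reward might even narrow the retention gap. Only the difference between arms is established.
- **That people who miss a survey are excluded.** The criterion on three assessments is an entry condition, and no passage removes anyone after randomisation.

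**Conclusion.** The point holds in a limited form. The declared principle and the named methods do not fit together at the loss that the article itself expects. Followed as written, without imputation, the between-group results would be completer comparisons on about 300 v 300 people, with retention of 33% v 50%. The possible bias is material but its direction is unknown. It is 0.06 to 0.15 SD in the illustrated follow-up t-test, which rests on an assumed r of 0.2 to 0.5 and monotone selection. It may be smaller or absent for change scores, and the trimming bound is 0.545 SD either way. The dropout rates are planning expectations; if actual loss is lower or balanced, the problem shrinks accordingly. This should be settled before outcome data are analysed, because a method chosen afterwards could be chosen by its result.

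**What to change.** - **Main change.** Replace the repeated-measures ANOVA with a likelihood-based mixed model for T1, T2 and T3 (available in SPSS as MIXED). Include all randomised participants, with arm, time, arm × time and income, and take the between-group estimate from the arm × time contrasts at T2 and T3.
- **Predictors of dropout.** Use T1 variables such as self-efficacy, stage of change, education and health literacy, either in the model or in multiple imputation. Imputation is the natural route for outcomes analysed as categorical.
- **Sensitivity.** The mixed model and standard imputation both assume that data are missing at random. Add one delta-adjusted or reference-based analysis for data missing not at random, with its settings fixed in advance.
- **Reporting.** Give retention by arm at T2 and at T3, and report the 300 v 40 JPY difference at T2 as a possible influence on response. A sentence stating that the three-assessment criterion applies at consent only, and never removes a randomised participant, would prevent misreading.

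The cost is revised analysis wording, one additional analysis and a wider confidence interval. No new participants or data are needed.
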